## Preliminary results

Between January 2006 and November 2006, 174 patients were eligible for the MONET – study. 108 patients were included in the study (recruitment rate 62%). The reasons for non-participation are listed in Table 1. Eight patients were excluded after randomization (no available histology (n = 5), unanticipated obesity (n = 1), technical failure of MR scanner (n = 1), age over 75 years (n = 1)). Three of the excluded patients were randomized in the control group and 5 in the MRI group. The characteristics of the 100 patients included so far in the MONET – study are summarized in Table 2. The mean age was 56.1 years (range 39.9 – 75.0 years). In these patients, a total of 109 lesions were detected: 108 lesions were detected on mammography and 1 lesion on ultrasound imaging. The majority of the lesions were microcalcifications and classified as BI-RADS 3 or 4. The histological diagnosis of the lesions included 2 non-representative, 9 normal breast tissue, 62 benign lesions, 21 non-invasive carcinomas and 19 invasive carcinomas. So, 35.4% of lesions turned out to be malignant (non-invasive and invasive) after LCNB. Forty-five patients were randomized into the MRI group and 55 into the control group.

**Table 1 T1:** Reasons for non-participation

**Reason non-participation**	**Number of patients (%)**
Unable to lie in prone position	1 (1.5%)
Metal implants	6 (9.0%)
Severe obesity	1 (1.5%)
Claustrophobia	16 (24.0%)
Geographical distance from teaching hospital to MRI too long	18 (27.0%)
Clinical indication for MRI of the breast	1 (1.5%)
Personal reasons	23 (35.0%)
**Total**	**66**

**Table 2 T2:** Characteristics of the first 100 patients included in the MONET – study

n	**100**
Referred from University Medical Center	**30**
Mean age (*range*)	**56.1 **(*39.9 – 75.0*)
Number of lesions detected on mammography	**108**
*density only*	*41*
*microcalcifications only*	*54*
*both*	*9*
*other*	*2*
*unknown*	*2*
BI-RADS classification mammography	
*3*	*45*
*4*	*47*
*5*	*11*
*unknown*	*5*
Number of lesions detected on ultrasound (*mammographically occult lesions*)	**1**
BI-RADS classification ultrasound	
*3*	*1*
*4*	*-*
*5*	*-*
*unknown*	*-*
Diagnosis LCNB	**113***
*non-representative*	*2 (1.7%)*
*normal breast tissue*	*9 (8.0%)*
*benign*	*62 (54.9%)*
*non-invasive carcinoma*	*21 (18.6%)*
*invasive carcinoma*	*19 (16.8%)*

* 4 lesions were sampled twice because of inconclusive results

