### Study design

The MONET – study is a randomized controlled trial. Patients will be recruited in 3 hospitals: two large community teaching hospitals and one University Medical Center. In all participating centers, Breast MRI is not part of routine clinical practice in the work-up of patients with suspicious nonpalpable breast lesions. We aim to include a total of 500 patients with nonpalpable, mammographically suspicious breast lesions who are referred for biopsy. After giving informed consent, patients will be randomized in the control group or the MRI group. Patients in the control group (n = 250) will undergo routine medical care. This includes mammography, ultrasound, and the lesion is sampled by means of large core needle biopsy. In case of malignancy (DCIS or invasive carcinoma), the lesion is surgically removed. The MRI group (n = 250) will undergo routine clinical care and in addition, contrast enhanced Breast MRI in the University Medical Center prior to the large core needle biopsy. The MRI scan will be performed within one week after mammography and before LCNB which will be performed within one week after MRI to avoid a diagnostic delay.

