### Data-analysis

We will compare the number of all biopsies and surgical procedures within one year after the first LCNB between the MRI group and the control group. To compare the diagnostic performance of MRI (in combination with mammography and ultrasound) and LCNB, a two-by-two table will be constructed in which the results of breast MRI in addition to mammography and ultrasound will be compared to the results of the histology of the tissue sampled at the large core needle biopsy. The positive predictive value will be calculated by dividing the number of correctly identified positives by the total number of positive Breast MRI's. The negative predictive value will be calculated by dividing dividing the number of correctly identified negatives by the total number of negative MRI's. Analyses will be performed for specific subgroups, i.e. microcalcifications and dense breast lesions on mammography. If the positive predictive value of mammography, ultrasound and Breast MRI is sufficiently close the positive predictive value of large core needle biopsy in patients with nonpalpable breast lesions in all patients or in a subgroup of patients, the biopsy in these patients may be replaced by MRI in the future. However, whether MRI can indeed replace LCNB in clinical practice will have to be assessed in a separate study.

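### Eight of 108 randomised women are removed, at least six for reasons arising after allocation; if this carries into the primary comparison, randomisation no longer protects it

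*Protocol article*

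**What the plan says.** Preliminary results starts from 174 eligible women, of whom "108 patients were included in the study (recruitment rate 62"%). It then reports the removals: "Eight patients were excluded after randomization (no available histology (n = 5), unanticipated obesity (n = 1), technical failure of MR scanner" (n = 1) and age over 75 (n = 1). By arm: "Three of the excluded patients were randomized in the control group and 5 in the MRI group". From there the excluded women leave the account: "The characteristics of the 100 patients included so far in the MONET – study are summarized in Table 2", and "Forty-five patients were randomized into the MRI group and 55 into the control group".

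Under Study design, "Patients in the control group (n = 250) will undergo routine medical care", while the MRI group also has "contrast enhanced Breast MRI in the University Medical Center prior to the large core needle biopsy". Only one arm is therefore scanned, and the scan falls between allocation and biopsy.

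Primary outcome counts all biopsies and all operations during a year of follow-up that starts at the LCNB. Data-analysis repeats this: "We will compare the number of all biopsies and surgical procedures within one year after the first LCNB", compared between the two groups. Neither section names an analysis set or says that the excluded women come back in.

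**The concern.** Randomisation makes the arms comparable as allocated. Removing women afterwards keeps that property only if the reason for removal cannot depend on the arm or on the outcome. Two of the stated reasons do not meet this condition.

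- **Scanner failure.** It can remove a woman only from the MRI arm. A comparable control woman stays in.
- **No available histology.** This arises after allocation and, in the MRI arm, after the scan. The primary outcome counts biopsies, so selecting on whether tissue was obtained is close to selecting on the outcome.

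Starting the clock at the first LCNB has a similar effect: a woman who never has an LCNB has no start date and no defined follow-up year.

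At stake is whether a difference in procedures can be attributed to MRI. The figures of 45 and 55 add to the difficulty, because a reader would take them as the randomised denominators.

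**Working it through.** **1. Counts (Preliminary results).**
- Eligible minus non-participants: 174 − 66 = 108, and 108/174 = 62%, as stated.
- Randomised to MRI: 45 + 5 = 50. Randomised to control: 55 + 3 = 58. Total 108.
- So 45 and 55 are the numbers left after exclusion. The word for inclusion is used for both the 108 and the 100.

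**2. Exclusion rates.** 5/50 = 10.0% in the MRI arm, 3/58 = 5.2% in control, 8/108 = 7.4% overall. Fisher's exact test of 5/50 against 3/58 gives p = 0.47.

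**3. Reasons.** Age over 75 is a baseline exclusion criterion under Subjects. Obesity may be one too, since weight above 130 kg is listed there. The other 5 + 1 = 6 arise after allocation. Reasons are not given by arm, but scanner failure must be in the MRI arm. The three control exclusions therefore come from obesity, age and histology, so at least one is missing histology. The possible splits of the five histology cases (MRI/control) are 4/1, 3/2 or 2/3. Missing histology thus occurred in both arms.

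**4. Power.** The plan states 90% power with 250 per arm for 23% versus 11%, two-sided 0.05. With mean rate 0.17:
- n per arm = [1.96·√(2·0.17·0.83) + 1.2816·√(0.23·0.77 + 0.11·0.89)]² / 0.12² = 204 (221 with continuity correction).
- At 250 per arm, power is 94.9%. The stated 250 and 90% are not reproduced, but the plan errs on the large side; that is a separate matter.
- At the observed exclusion rates, 250 × 0.90 = 225 MRI and 250 × 55/58 = 237 control women would remain, with power 93.2%. Power is not the problem.

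**5. Possible shift in the effect.** Suppose the planned rates hold among retained women. Let e_m and e_c be the event rates among the excluded, with fractions f_m = 0.100 and f_c = 3/58 = 0.0517. Over all randomised women:

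D = [(1 − f_c)·0.23 + f_c·e_c] − [(1 − f_m)·0.11 + f_m·e_m]

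| Assumption about excluded women | Control | MRI | D (points) |
|---|---|---|---|
| All at 23% | 23.0% | 12.2% | 10.8 |
| All excluded MRI women have the event, no excluded control women do | 21.8% | 19.9% | 1.9 |
| The reverse | 27.0% | 9.9% | 17.1 |

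For the one exclusion that is certainly arm-specific (1/50 = 2% of the MRI arm, taken at 23%), the MRI rate is 0.98 × 11% + 0.02 × 23% = 11.24%, and D = 11.8 points.

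**The case against.** The strongest reply is that Preliminary results is a baseline description of early recruits, not an analysis plan. Data-analysis compares the two groups without any per-protocol restriction, and the analysis set may be defined in a fuller document that is not shown. This stands in part: a reader might infer that the final comparison is certain to omit these women, and the text does not say so. It does, however, report a practice already applied, with the women called excluded and the denominators changed to match, and nothing in the article reverses it.

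Further points stand as limits on the concern:

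- Only one exclusion is provably specific to the MRI arm. A reader might infer that MRI drove the missing histology, but no reason is given for it, missing histology need not mean that no biopsy was done, and at least one such case was a control. Secondary outcome expects every patient to have an LCNB.
- A reader might take 10.0% against 5.2% as evidence of bias. With p = 0.47 it is not; the objection is to the rule.
- A reader might infer that the 250 per arm is being eroded. Study design aims to include 500, and the article also calls the 100 left after exclusion included, so recruitment may continue until 500 remain.
- A reader might scale the 12 points by the 35.4% malignant lesions and set the exclusions against a much smaller effect. Sample size states 23% and 11% for women with suspicious lesions, so the plan's own effect is 12 points.
- Removing true baseline eligibility failures is a recognised practice if the decision is blind to arm and the rule is the same in both. The article does not say whether that was so.
- The choice of clock moves the window little for women who do have an LCNB: in the MRI group, the scan is due within one week of mammography and the biopsy within one week of the scan. The difficulty is confined to women who have none.

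**Conclusion.** The point holds as a conditional one. The article removes 8 of 108 randomised women and reports the remainder as the numbers randomised. At least six removals arise after allocation; one reason can act in the MRI arm only, and another lies close to the outcome. If the same exclusions apply in the primary comparison, as the text implies, that comparison is no longer protected by randomisation.

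The likely size is modest: 10.8 instead of 12 points if every excluded woman had the control rate. The bounds of 1.9 and 17.1 points are extremes and should not be read as expected values, although the lower one falls below the 5% that Sample size treats as the threshold of clinical relevance. The direction is unknown.

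These figures assume that the exclusion rates of the first 108 women persist, that the planned 23% and 11% hold among retained women, and that the proportion needing more than one operation, on which the trial was sized, stands in for the procedure counts to be analysed.

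**What to change.** - **Primary analysis set.** Analyse the primary outcome in all randomised women in the assigned arm, including MRI-arm women who were not scanned and women without histology.
- **Clock.** Count procedures for one year from randomisation, so that a woman without an LCNB contributes the procedures she actually had.
- **Women already excluded.** Retrieve their procedures from hospital records.
- **Eligibility failures.** Women who failed a baseline criterion (age, possibly weight) may be left out only if this is judged blind to arm and by the same rule in both arms. Write that rule down.
- **Predictive values.** Limit the set with both MRI and histology to the PPV and NPV analysis.
- **Reporting.** Give 50 and 58 as the numbers randomised to MRI and control, with exclusion reasons by arm.

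The cost is some wording and record retrieval for eight women so far. The downside is slight dilution from unscanned women: 11.8 instead of 12 points for the one known scanner failure. No patient's care changes, and with recruitment planned to 2008 the rule can be fixed before the comparison is made.

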## Discussion

The purpose of the MONET – study is to evaluate whether performing contrast-enhanced Breast MRI in addition to mammography and/or ultrasound in patients with nonpalpable suspicious breast lesions will improve breast cancer management, i.e. to reduce the number of surgical procedures and/or the number of large core needle biopsies.

Many well conducted large clinical studies have been performed on the diagnostic performance of Breast MRI [5,6]. Only very few studies assessed the impact of Breast MRI on patient management. Two large observational studies have been performed to assess the value of Breast MRI for preoperative staging of patients with breast cancer [22,27]. The underlying assumption of both studies is that preoperative staging of the breast with MRI leads to the detection of mammographically occult multifocal and multicentric breast cancer, and that by removing these additional malignant lesions, the breast cancer recurrence rate could be reduced. Fischer et al compared the recurrent cancer rate in patients who did and did not undergo preoperative staging of the breast with MRI [22]. The reported recurrent cancer rate was indeed lower in the MRI group (1.2% (1/86)) than in the non-MRI group (6.5% (9/138)) after a mean follow-up time of 41 months. The percentage of contralateral tumors was lower in the MRI group as well: 1.7% (2/121) versus 4.0% (9/225). These differences were found to be statistically significant (p < 0.05) [22]. The recurrent cancer rate will also be assessed in the MONET – study: 5 years after completion of the MONET – study, the difference in recurrent cancer rate between patients from the MRI group and the control group will be assessed. Another study evaluated the change in surgical treatment after preoperative staging with MRI in patients with breast cancer [27]. Of the 267 patients that were scheduled for breast conserving therapy, the surgical plan of 69 patients (26%) was altered to more extensive surgery based on information obtained from preoperative staging with MRI. In 44 of these patients (64%) the alteration was considered to be appropriate based on pathological verification of malignancy in the surgical specimens [27]. Both authors advise preoperative staging with contrast-enhanced MRI in patients with breast cancer [22,27].

Randomized clinical trials assessing the therapeutic consequences of performing preoperative Breast MRI have not yet been performed. Moreover, the above mentioned studies included a mixture of patients with palpable and nonpalpable breast tumors. We believe that the nonpalpable lesions are the most challenging to remove in one attempt since these lesions cannot be seen or palpated at the end of the preoperatively inserted wire and the number of these nonpalpable lesions in increasing due to the widespread introduction of screening programs.

In conclusion, the aim of the MONET – study is to assess the diagnostic and therapeutic consequences of performing MRI of the breast in addition to mammography and ultrasound in patients with nonpalpable suspicious breast lesions.

## Abbreviations

MRI Magnetic Resonance Imaging

MONET ***M***R mammography ***O***f ***N***onpalpable Br***E***ast ***T***umors

LCNB Large Core Needle Biopsy

95% CI 95% Confidence Interval

DCIS Ductal Carcinoma in Situ

BI-RADS Breast Imaging Reporting and Data System

kg Kilograms

T Tesla

TE Echo Time

TR Repetition Time

msec milliseconds

SPAIR Spectral Presaturation Attenuated by Inversion Recovery

FOV Field-of-View

mm millimetres

mmol millimols

DTPA Gadopentetate Dimeglumine

PACS Picture Archiving and Communications System

3D 3-dimensional

